# Study protocol for ACTIVE study: safety and feasibility evaluation of external ventricular drainage with ACTIVE fluid exchange in intraventricular hemorrhage—a phase 2, multi-center, randomized controlled trial

**DOI:** 10.1186/s13063-022-07043-9

**Published:** 2022-12-29

**Keywords:** Intraventricular hemorrhage, External ventricular drainage, IRRAflow, Irrigation, Aspiration

## Abstract

**Background:**

Primary intraventricular hemorrhage (IVH) or IVH secondary to intracerebral (ICH) and subarachnoid hemorrhage (SAH) are known to have a very poor prognosis, with an expected mortality between 50 and 80% (Hinson et al. Current Neurology and Neuroscience Reports 10:73–82, 2010). Clearance of IVH might improve patient outcome.

**Methods:**

The study is designed as an investigator-initiated, comparative, prospective, multi-center, 1:1 randomized phase 2 trial evaluating the efficacy and safety of active irrigation in external ventricular drainage (intervention arm—IRRAflow) compared to passive external ventricular drainage (control arm—EVD).

The trial will enroll 58 patients with primary or secondary IVH. Major eligibility criteria include age ≥18 years of age, IVH documented on head CT or MRI scan (Graeb score ≥3), need of cerebrospinal fluid drainage, deterioration of consciousness or medical sedation at the time of enrollment, and indication for active treatment evaluated by the treating physicians. Exclusion criteria included patients with fixed and dilated pupils and pregnant or nursing women.

The primary endpoint of the study is catheter occlusion evaluated by time to first observed occlusion from VC placement. Secondary endpoints include clearance of ventricular blood as measured by head CT scan, rates of catheter-related infection and shunt dependency, length of intensive care unit stay, functional status—Extended Glascow Outcome Scale (eGOS) and modified Rankin scale (mRS) at discharge to rehabilitation and 90 days—and mortality rates at 30 days and 90 days.

**Discussion:**

With no standardized treatment for IVH and a poor prognosis, new treatments are needed. IVH patients often need CSF drainage to treat hydrocephalus and to decrease ICP. Standard treatment with passive external ventricular drainage is related to an increased risk of infections which is found in up to 22% of treated cases. The passive VC is known to have a risk of occlusion and is seen in 19–47% of the cases.

We hypothesize that the use of active fluid change using the IRRAflow system will be safe and feasible and will reduce the occlusion and infection rates in patients with IVH.

**Trial registration:**

ClicalTrials.gov NCT05204849. Registered 15 December 2021. Updated 24 January 2022

**Supplementary Information:**

The online version contains supplementary material available at 10.1186/s13063-022-07043-9.

## Background

Primary intraventricular hemorrhage (IVH) or IVH secondary to intracerebral hemorrhage (ICH) and subarachnoid hemorrhage (SAH) with extension to the ventricles are known to have a very poor prognosis, with expected mortality between 50 and 80% [1]. Yet, therapy directed at ameliorating intraventricular clot has been limited. IVH often results in increased intracranial pressure (ICP) by direct mass effect, by obstruction, and further by creating edema around the hematoma. These conditions can be complicated by hydrocephalus caused by CSF malabsorption [2] or obstruction of CSF pathways. Further secondary brain injury is related to the clotting cascade after endothelial damage and hemoglobin breakdown [3]*.* Thrombin causes inflammatory cells to infiltrate the brain, proliferation of mesenchymal cells, formation of brain edema, and scar tissue [3]*.* Thrombin binds to protease-activated receptors *(1)* and activates the central nervous system microglia and complement cascade. As a result, multiple immune pathways are activated, which contributes to apoptosis and necrosis. Heme influx in neurons after endothelial damage leads to iron release and neuronal insult [3].

CSF drainage is a key factor in maintaining acceptable ICP levels to prevent secondary brain damage. There are multiple approaches to facilitating CSF drainage and monitoring ICP. A ventricular catheter (VC) inserted into the lateral ventricle allows for drainage of CSF, but complication rates are high. VC occlusions in patients with IVH have been reported in 41% [4], of these 19% are having at least one VC replacement [4]. VC-related infection rates are found to be 10% for bacterial ventriculitis [5, 6].

The aim of this study is to evaluate the safety and feasibility in the use of active fluid exchange in the treatment of intraventricular hemorrhage.

## Methods and study design

This current phase 2 and feasibility study evaluates the IRRAflow system. A closed system VC with active irrigation and aspiration in comparison to standard passive external ventricular drainage (Fig. 1). We hypothesize that closed system active irrigation will be safe to use and will reduce the occlusion and infections rates and increase clearance rate and clot removal. The framework of the trial is to test the superiority of IRRAflow compared to EVD treatment. This manuscript is based on protocol version 4.0 dated 16th of January 2022. Important amendments to the protocol will be added and shown in clinicaltrials.gov.

**Fig. 1 Fig1:**
[figure not shown]
The IRRA*flow* system consists of a dual lumen catheter for irrigation and aspiration respectively (courtesy of IRRAS)

The study is an investigator-initiated, prospective multi-center, 1:1 randomized, comparative phase 2 trial evaluating the efficacy and safety of active irrigation external ventricular drainage (intervention—IRRAflow) compared to passive external ventricular drainage (control—EVD) (Fig. 2). The investigators are unblinded for the treatment, but there is blinding concerning evaluations of endpoints where possible.

**Fig. 2 Fig2:**
[figure not shown]
Intervention arm (IRRAflow) and control arm (external ventricular drainage, EVD)

The trial will enroll an expected sample size of 58 patients (sample size calculation see “sample size and statistical considerations”). The enrollment period is estimated to be 24 months from the date of the first patient enrolled. Patients will be followed for 3 months with expected trial termination after 27 months from initiation. The study setting is academic hospitals and data will be collected in different neurosurgical departments in Denmark (Aarhus University Hospital and Odense University Hospital).

Intraventricular fibrinolysis (IVF) is prohibited until failure of the catheter. IVF can be administrated after an occlusion of the catheter has appeared.

### The IRRAflow device

The IRRAflow system performs active, controlled fluid exchange, based on the notion that it is faster to wash out IVH, compared to gravity drainage alone. IRRAflow combines periodic, controlled irrigation and aspiration of the catheter probe with neutral physiological fluids. The continuous perfusion cleans the entire inner catheter probe’s surface while the fluid movement helps to disrupt potential clot or bacteria colony formation on the catheter probe’s intracranial external surface, thereby minimizing the problems associated with passive drainage: blockage and infection. IRRAflow perfusion is combined with continuous ICP monitoring that includes safety alarms.

#### Primary endpoint

Catheter occlusion evaluated by hours to first observed occlusion from VC placement

#### Secondary endpoints

Clearance of ventricular blood measured by the absolute volume of blood in ml on head CT scansRate of catheter-related infectionLength of ICU stayRate of shunt dependencyFunctional status—extended Glascow outcome scale (eGOS) and modified Rankin scale (mRS) at inclusion, discharge to rehabilitation and 90 daysMortality rates at 30 days and 90 days

#### Exploratory endpoints

Duration of ventricular drainage (EVD and IRRAflow) in daysProcedure complicationsDevice-related complicationsProcedure timeRate of revision procedures of the ventricular catheterRate of occurrence of repeated hemorrhagic eventsNumber of flushes requiredTotal cost of the procedure

#### Trial overview

The patient population for this study will be comprised of up to 58 patients with the diagnosis of primary intraventricular hemorrhage or secondary IVH from SAH or ICH with an intraventricular breakthrough.

### Ethics

Patient selection criteria are established according to clinical, radiologic, and neurologic components. Patients who meet all the inclusion criteria and none of the exclusion criteria will be eligible for study participation. Candidates for enrolment in the trial will typically be severely disabled by the acute neurological injury occurring due to hemorrhagic stroke. Patients will be in a state of coma or medically sedated and often intubated leaving them physically and/or mentally incapacitated, legally incompetent, and unable to make a proper conscious decision about trial participation and therefore also unable to provide informed consent at the appropriate time of enrollment and guidelines on “acute study” conduct will be followed. The trial investigators will subsequently obtain a written informed consent from the patient or a relative to the patient upon first possible notice in accordance with §§3-5 in the Danish Law on Health Research Ethics (consent form see Additional file 1). No biological samples are taken from the patients nor stored, used, or analyzed in the study and therefore no consent for biological samples is required.

The recruitment strategy is based on a patient enrollment throughout the day. The on-call doctor at each center is instructed in contacting the coordinating investigator when a suitable patient has been admitted to the hospital. The coordinating investigator oversees the randomization of the patient.

#### Inclusion criteria

Age >18 years of ageIntraventricular hemorrhage documented on head CT or MRI scan. The scan must be no older than 24 hIntraventricular hemorrhage Graeb score ≥3 points [7]Need of cerebrospinal fluid drainage (<24 h) deemed by treating physicianDeterioration of consciousness or under medical sedation at the time of enrollment causing the patient to be mentally and/or physically incapacitated and legally incompetent in the decision of inclusion (“acute study” conduct)Indication for active treatment evaluated by the treating physiciansUse of validated anti-conception for fertile female participants in concordance with guidelines provided by the Danish Health and Medicines Authority or a negative urine HCG test

#### Exclusion criteria

Patient with fixed and dilated pupilsPregnant or nursing women (fertile female participants are required to take a validated pregnancy test for evaluation of pregnancy)

#### The randomization procedure

Patients eligible for inclusion following the above-mentioned criteria will be randomized in a 1:1 fashion for EVD or IRRAflow. The allocation sequence is allocated by the RedCAP administrator at Aarhus University. The randomization procedure is performed using the RedCAP randomization module. The randomization is performed by the coordinating investigator in the trial. Randomization will be carried out upon arrival to the operation room and informed consent will be obtained at the first possible occasion after VC placement (Fig. 3).

**Fig. 3 Fig3:**
[figure not shown]
ACTIVE study flowchart

#### Ventricular catheter placement

VC placement is a standard neurosurgical procedure, and all patients will receive catheters placed according to the standard procedure for EVD placement in both groups. The procedure is performed neuronavigational guided to ensure correct placement and safety for the patient. The catheter is placed in the lateral ventricle containing the least blood and always intended to be placed in CSF outside of the hematoma. The IRRAflow catheter will be placed by reverse tunneling (Fig. 4A–C), whereas the standard EVD will be placed on a bolt.

**Fig. 4 Fig4:**
[figure not shown]
**A** The tunneled ventricular catheter (VC). **B** Placement of the VC in the ventricular system. **C** The result where the VC is attached, and the skin is sutured

#### Device training

All investigators, co-investigators, and study personnel will undergo standardized training in study conduct and procedures, including the use and operation of the IRRA*flow* device, prior to study participation. IRRAflow training and certification will be conducted by a qualified IRRAS associate or designee.

#### Follow-up assessments

After placement of the VC, the patients in the two arms will receive the same treatment and monitoring. They will be admitted to the intensive care unit and later transfer to the stationary neurosurgical department before discharge to a rehabilitation facility. Patients will be followed closely regarding the primary, secondary, and exploratory endpoints. During the admission period, the patients will be followed with a CT scan at day 0, day 2, day 4, day 6, and day 8 to evaluate the size of the hematoma using CT volumetrics.

A scheduled follow-up will be applied for all included patients including a clinical status at the time of inclusion, discharge, and 3 months post-procedure. The follow-up will include GCS and mRS at inclusion, discharge, and 3 months. Furthermore, eGOS will be evaluated at discharge and 3 months. The rate of shunt dependency, adverse events, and serious adverse events will be evaluated continuously during the inclusion period. Mortality rates will be evaluated at 30 days and 3 months.

All patients will receive best practice care following trial exclusion or termination. Post-trial care will be independent of trial participation and similar to the care offered to patients who were not enrolled or withdrew consent. Patients who are harmed during the trial will not be offered compensation, which is specific for the trial. However, patients might be eligible for compensation under similar rules and conditions as patients who are not enrolled in the trial as defined by Danish law (Patienterstatningen).

#### Patient withdrawal and lost to follow-up

A patient or patients relative may elect to withdraw from this clinical study at any time. The patient or the patient’s relative should notify the investigator of the request to withdraw. The investigator should encourage patients to return for all required follow-up visits and request that they return for the withdrawal visit.

All patients who withdraw from the study will complete an end-of-study visit. No further visits will be required by the patient once the end-of-study visit is complete. A patient has the right to withdraw from the trial at any time and for any reason without prejudice to his or her future medical care by the physician or the institution. Trial withdrawal by a patient or their LAR specifically means withdrawal of consent from further participation in the trial. Patients who withdraw consent after enrollment will be evaluated to the time of withdrawal, and withdrawal of consent precludes any further trial-related treatment or data collection. LAR may also withdraw consent. At a minimum, every effort should be made to document patient outcome at the time of trial withdrawal.

All patients will be expected to continue in the trial through the final follow-up assessment except in the event of death or upon the patients’ or patients’ relative written request for early withdrawal from the clinical trial.

#### Data management

In the ACTIVE study, all data will be entered electronically and stored in the RedCAP database. Data will be obtained at the site treating the patient and entered directly into the electronic database. Original study forms will be kept in a file at the participating site. Confidentiality of personal information regarding enrolled patients will be kept securely at the study site. All local databases will be secured by password-protected access systems.

#### Sample size and statistical considerations

The sample size of the study was determined based on the primary outcome. We considered a two-sided log-rank test for comparison of the time-to-catheter occlusion between the two treatment groups. Furthermore, we assumed an equal length of follow-up together with an occlusion risk of 10% and 35% in the intervention and control groups. Patient mortality was assumed to be independent of the considered time to catheter occlusion and to correspond to a 30% dropout. We used a significance level of 20% due to the exploratory nature of the study. Then, for a power of 80%, Schoenfeld’s approach resulted in a required sample size of 58 (i.e., 29 subjects with drain per treatment group).

Data will be analyzed according to the intention-to-treat principle. For the primary outcome (time to catheter occlusion), time-to-event analysis will be used, in which drains are considered the basic experimental units. Times corresponding to drains without occlusion during follow-up will be considered censored. Especially, since catheter occlusion is independent of patient mortality, patient death is treated as a censoring event. Time to occlusion will be described by Kaplan-Meier plots and investigated by Cox regression. Estimated beneficial treatment effects with a two-sided *p*-value ≤ 20% will be considered an interesting finding worth further investigation.

Further outcome measures (secondary/exploratory) will be used for descriptive and exploratory purposes only; no formal statistical hypotheses will be tested.

Secondary endpoints (subject-based unless otherwise specified) will be handled as follows:

Kaplan-Meier estimates and Cox regression will be used to describe the time to recurrence of hemorrhage and time to death (with a follow-up time of 3 months).

Occurrence of catheter-related infections and shunt dependency will be reported as proportions, and length of stay in ICU will be reported as means. Clearance of ventricular blood will be described with the help of linear mixed effect models. Measures of functional status will be dichotomized and analyzed by baseline-adjusted logistic regression. All estimates will be reported together with corresponding confidence intervals (CIs).

Exploratory endpoints (mainly drain-based) will be handled as follows:

Proportions and CIs will be reported for technical success, procedure success, and necessity of revision procedures. Procedure time, duration of VC in place, and number of required flushes will be described by means and CIs.

Reported CIs will include a Bonferroni adjustment to maintain the family-wise coverage probability at 95%.

We expect based on our prior experiences that the proportion of missing values in this study will be very low and that missing values occur completely random. All statistical analyses will be run as complete case analyses.

For early safety monitoring, an interim analysis is done when 20 subjects have been enrolled in the study (10 subjects per arm). The analyses will be performed in an intent-to-treat fashion.

Monitored safety outcomes are mortality as well as the total number of adverse and serious adverse events related to catheter treatment (infections, bleedings in relation to intervention, displacements of catheters, catheter misplacement). For *p*-values below 20%, an early stop of the study will be considered (non-binding); otherwise, the study continues until the study end.

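### The primary analysis names the drain as its unit, which conflicts with randomisation by patient, a first-occlusion endpoint and a sample size counted in subjects

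*Protocol article*

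**What the plan says.** All references are to the protocol article.

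- **Randomisation** (The randomization procedure): eligible patients "will be randomized in a 1:1 fashion for EVD or IRRAflow".
- **Endpoint** (Primary endpoint): "Catheter occlusion evaluated by hours to first observed occlusion from VC placement".
- **Size** (Sample size and statistical considerations): a total of 58, given as "29 subjects with drain per treatment group".
- **Primary analysis** (same section): after a commitment to intention to treat, "time-to-event analysis will be used, in which drains are considered the basic experimental units". Censoring follows the same unit: "Times corresponding to drains without occlusion during follow-up will be considered censored". The methods are given as "Time to occlusion will be described by Kaplan-Meier plots and investigated by Cox regression".
- **Contrast** (same section): the next block opens "Secondary endpoints (subject-based unless otherwise specified) will be handled as follows", and the exploratory endpoints are then described as mainly drain-based.
- **After an occlusion** (Methods and study design, below Figure 2): fibrinolysis is barred until the catheter fails, then "IVF can be administrated after an occlusion of the catheter has appeared".
- **Replacement is foreseen**: the Background reports catheter occlusion in 41% of patients with IVH and replacement in 19% of these, and the revision rate is an exploratory endpoint.

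**The concern.** A first-occlusion endpoint in randomised patients gives one time per patient. A drain-based analysis gives one time per drain, and some patients will have more than one. The article distinguishes subject-based from drain-based outcomes, so the choice of drain for the primary outcome does not look like loose wording.

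If later drains were included, three things would follow.

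1. Drains from one patient share the same haemorrhage. An analysis that treats them as independent can understate the standard error.
2. Later drains were not randomised. Those placed for occlusion exist because an earlier drain failed, so they would come mostly from the arm that occludes more. They may also be exposed to fibrinolysis, which is withheld before the first occlusion. Neither fact fits an intention-to-treat comparison.
3. A hazard over all drains is a different quantity from the time to first occlusion for which the trial was sized.

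At stake is which records enter the trial's one formal test.

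**Working it through.** **Step 1. Which unit does the sample size use?** Inputs from the sample size section: occlusion risks 10% and 35%, two-sided level 20%, power 80%, 30% dropout, 1:1 allocation, Schoenfeld's method.

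- Hazard ratio = ln(0.90)/ln(0.65) = 0.2446
- Events = 4 × (1.2816 + 0.8416)² / (ln 0.2446)² = 9.09
- Mean risk = (0.10 + 0.35)/2 = 0.225
- Subjects before dropout = 9.09/0.225 = 40.4
- Subjects after dropout = 40.4/0.70 = 57.7, rounded up to 58

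This reproduces the stated 58 with one drain per subject. Expected events are 58 × 0.70 × 0.225 = 9.1, and power is 80.1%.

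**Step 2. How many drains might be replaced?** The Background's 19% can be read in two ways. As worded, it is 19% of occluded cases. If it is a share of all patients, it is 19/41 = 46% of occluded cases.

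**Step 3. Where would later drains arise?** At the planned risks, 35/(35 + 10) = 78% of first occlusions fall in the control arm. Replacements for occlusion would therefore come mainly from that arm.

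**Step 4. What happens to the 20% level?** This was simulated with no treatment effect: 29 patients per arm, 30% independent death, and each drain timed from its own placement. Within-patient correlation enters through a gamma frailty. The test is a log-rank test that treats drains as independent. The frailty variances and replacement patterns are assumptions. The first row rests on 6000 runs per setting (Monte Carlo SE about 0.5 points), the others on 3000 (about 0.7 points).

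| Occluded drains replaced | Occlusion risk, both arms | Most drains per patient | Frailty variance | Rejection, all drains | Rejection, first drain only |
|---|---|---|---|---|---|
| 19% | 22.5–35% | 2 or 4 | 0 to 2 | 20–22% | 20–21% |
| 46% | 22.5% | 2 | 0 / 1 / 2 / 4 | 21.3 / 21.5 / 22.4 / 24.3% | 20.2 / 20.3 / 21.1 / 20.9% |
| all | 22.5% | 2 | 0 / 1 / 2 / 4 | 20.9 / 25.0 / 24.6 / 25.2% | 19.7 / 22.3 / 20.0 / 19.8% |
| all | 22.5% | 5 | 0 / 1 / 2 / 4 | 19.8 / 24.6 / 29.9 / 36.5% | 19.4 / 19.8 / 19.8 / 19.8% |
| all | 35% | 5 | 1 / 2 | 28.9 / 32.9% | 20.5 / 20.8% |

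A separate run at 35% risk, with up to four drains, every occluded drain replaced and variance 2, gave 35%.

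In the settings of the last four rows, a patient-clustered variance brought the all-drain rejection rate to 19.8–23.4%. That deals with the correlation. It does not make later drains randomised.

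On the Background's figures, the 58 patients supply about 60 to 66 drains, so there are few extra records. The simulation shows about 11 first events, against 9.1 in Step 1, because patients who die still contribute time until death.

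**The case against.** The strongest reply is that the article never says replacement drains are analysed. The endpoint speaks of a first occlusion, and the sample size pairs each subject with a drain. On that reading, the drain is merely the object being timed, and there is one per patient. This is tenable. A reader might infer that repeated drains from one patient will certainly be counted as independent evidence; the documents do not support that as a fact. Nor do they say that every occluded drain is replaced. The Background's figures point to fewer, and the plan also provides for flushing and for fibrinolysis after occlusion.

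A second reply is that the absence of a clustering term proves nothing. That is correct. A condensed article may leave variance estimation to the full protocol or analysis plan, so the silence is no fault.

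A third reply is that a few points on a deliberately lenient 20% exploratory level change little. That also has force, and it lowers the severity.

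The stated unit remains. If one drain per patient is intended, the sentence is misleading and should say so. It could also be argued that the endpoint refers to each catheter's own placement and its own first occlusion. That would align the endpoint with the drain, but the conflict with randomisation and with the subject-based sample size would remain.

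**Conclusion.** The unit sentence is wrong as written. It conflicts with randomisation by patient, the first-occlusion endpoint, intention to treat and the sample size.

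The effect on the 20% level cannot be fixed from the documents:

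- essentially none without within-patient correlation;
- about 0 to 4 points if 19% to 46% of occluded drains are replaced;
- about 12 to 15 points if every occluded drain is replaced repeatedly, at 35% risk in both arms and frailty variance 2; the most extreme setting run (22.5% risk, variance 4, up to five drains) gave 16.5 points.

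A reader might conclude that the test clearly fails to hold its level. That needs replacement rates above those in the Background and frailty variances that have no source in the documents. A reader might also conclude that 58 is too few, but that figure already assumes one drain per subject. The problem of non-randomised later drains, possibly exposed to fibrinolysis, would exist at any replacement rate above zero if such drains were included. Its size was not estimated.

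Severity: should be fixed before the analysis, but does not undermine the trial.

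**What to change.** Replace the unit sentence and the per-drain censoring sentence. The randomised patient is the unit, with one record per patient: time from placement of the first study catheter to its first observed occlusion, censored where no occlusion is seen. Report later drains descriptively, or in a supportive all-drain analysis with patient-clustered variance, labelled as not a randomised comparison.

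The cost is a short text change. The sample size stays at 58, with about 9 expected events and 80% power, and no new data are needed.

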## Discussion

With no standardized treatment for IVH and a poor prognosis, new treatment modalities or methods are highly needed. We present a randomized, interventional, clinical phase 2 trial testing a new and innovative intervention, active fluid exchange using the IRRAflow closed irrigation system in comparison to the standard passive external VC for IVH Graeb score 3 or above.

The importance of CSF drainage in patients with IVH is well known in the treatment of acute hydrocephalus and to decrease ICP. Removal of potential cytotoxic material is an added benefit. However, standard treatment with passive external ventricular drainage is known to be related to an increased risk of infections such as ventriculitis and is found in up to 22% of the cases treated with EVD [8, 9]. Furthermore, the passive VC is known to have a risk of occlusion in IVH patients due to blood clotting and is seen in 19–47% of the cases [8].

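### Independence of occlusion and death is stated as fact to justify censoring, so the Kaplan-Meier description of the primary outcome overstates the occlusion risk patients experience

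*Protocol article*

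**What the plan says.** The primary endpoint is "Catheter occlusion evaluated by hours to first observed occlusion from VC placement". Under Sample size and statistical considerations, the trial is sized on a "two-sided log-rank test for comparison of the time-to-catheter occlusion between the two treatment groups", with occlusion risks of 10% (intervention) and 35% (control). Mortality is entered as a 30% dropout and described there as assumed to be independent of occlusion.

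Two sentences in the analysis paragraph of the same section fix the censoring:

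- "Times corresponding to drains without occlusion during follow-up will be considered censored"
- "since catheter occlusion is independent of patient mortality, patient death is treated as a censoring event"

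Kaplan-Meier plots and Cox regression are the methods named for this outcome. For secondary outcomes, "Kaplan-Meier estimates and Cox regression will be used to describe the time to recurrence of hemorrhage and time to death".

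The rationale elsewhere in the article links blood to both events. The Discussion says that "the passive VC is known to have a risk of occlusion in IVH patients due to blood clotting". The Abstract suggests that clearing the ventricles may improve outcome. The Discussion also reports, from a cited trial of alteplase against saline, lower case fatality with alteplase and an association between clot removal and better mRS.

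**The concern.** What is an assumption in the sample size paragraph becomes, in the analysis paragraph, a statement of fact that justifies the censoring rule. Nothing in the article supports it. If ventricular blood contributes both to occlusion and to a poor outcome, as the rationale suggests, the two events are probably related.

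Two things are at stake:

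- **The described risk.** Death and drain removal end the possibility of occlusion; they do not merely hide it. Censoring them makes one minus Kaplan-Meier a risk in a setting where nobody dies and no drain comes out. A reader who takes the curve as the share of drains that occlude will read it too high.
- **The treatment comparison.** If the two events share a cause and mortality differs between arms, censoring at death is informative and can shift the Cox hazard ratio. Mortality at 30 and 90 days is a secondary endpoint, so the trial itself allows for a difference.

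The same descriptive problem applies to recurrent haemorrhage, which death also precludes.

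**Working it through.** **1. The plan's own figure.** Inputs from Sample size and statistical considerations: risks 10% and 35%, two-sided alpha 20%, power 80%, dropout 30%. Allocation is 1:1.

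- HR = ln(0.90)/ln(0.65) = 0.245, so ln HR = -1.408
- Events = 4 × (1.282 + 0.842)² / 1.408² = 9.09
- Mean event probability = (0.10 + 0.35)/2 = 0.225, and 9.09/0.225 = 40.4
- Allowing for dropout: 40.4/0.70 = 57.7, rounded up to 58

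The stated 58 reproduces. It does so with 10% and 35% taken as risks before death and mortality applied separately, which is the Kaplan-Meier scale.

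**2. From Kaplan-Meier risk to experienced proportion.** Assume constant, independent hazards over the period the drain is in place. With a = -ln(1 - occlusion risk) and b = -ln(1 - mortality in that period), the cumulative incidence is a/(a+b) × (1 - exp(-(a+b))).

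Control arm at 30% mortality: a = 0.431, b = 0.357, so 0.547 × (1 - 0.65 × 0.70) = 0.547 × 0.545 = 29.8%.

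| Mortality while drain in place | Control (KM 35%) | Intervention (KM 10%) | Difference (KM 25 points) |
|---|---|---|---|
| 10% (assumed) | 33.3% | 9.5% | 23.8 |
| 20% (assumed) | 31.6% | 9.0% | 22.6 |
| 30% (planning value, all in this period) | 29.8% | 8.4% | 21.4 |

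In the control arm the overstatement is about 2 to 5 points. Removal without occlusion would widen it, but the article gives no removal rate, so I put no figure on that.

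**3. The hazard ratio.** Large simulations with no true device effect on occlusion, control occlusion risk 35%, and a shared log-normal severity factor acting on both occlusion and death. Every input here except the 35% is assumed.

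| Mortality, lower arm vs higher arm | Log-SD 1 | Log-SD 1.5 |
|---|---|---|
| 10% vs 15% | 1.02 | 1.03 |
| 20% vs 30% | about 1.04-1.05 | 1.09 |
| 30% vs 50% | about 1.11-1.12 | about 1.25 |

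With no shared factor the hazard ratio is 1.00 whatever the mortality difference. With a shared factor but equal mortality it is also 1.00. The ratio is for the lower-mortality arm against the other, so a value above 1 makes the lower-mortality arm look worse on occlusion. A gamma-distributed shared factor (variance 1 to 4) with the death hazard halved gives 1.06 to 1.34 at 30-50% control mortality.

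**4. Precision.** With 9.09 events, SE(ln HR) is about 2/√9.09 = 0.66. The 80% interval, which matches the 20% threshold, spans a factor of exp(1.282 × 0.66) = 2.3 each way. A drift to 1.25 is ln(1.25)/0.66 = 0.34 of a standard error, against a design hazard ratio of 0.245.

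**The case against.** The strongest reply is that censoring at death in a log-rank or Cox analysis is the standard cause-specific comparison, that Kaplan-Meier estimates the very quantity the trial was sized on, and that cumulative incidence plots and sensitivity models belong in an analysis plan that is not shown. The sample size paragraph also uses the word assumed.

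Much of this stands. The primary test should not change, and the absence of extra analyses from a condensed article is not in itself a fault. What remains is a rule the article does state: independence is given as the reason for the censoring, without support and against the article's own rationale.

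A reader might also infer more than the documents support:

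- **That the sizing used the wrong risks.** It did not. Step 1 shows that 10% and 35% are on the Kaplan-Meier scale.
- **That the gap is far larger because Background gives 50-80% mortality.** That range has no time window. Drainage duration is counted in days and the last scheduled CT is at day 8. Deaths after the drain is out do not compete, so the whole range cannot be placed in the drain-in-place period.
- **That the hazard ratio is materially biased.** This needs both a shared cause and a mortality difference, and the sizes rest on assumed inputs.
- **That drains come out sooner on IRRAflow because blood clears faster, so removal is informative by arm.** The article expects faster clearance but states no removal criterion. Removal competes with occlusion; its dependence on arm is not documented.
- **That the article says those who die are those most likely to occlude.** It does not. The link is an inference from its rationale, and the cited alteplase trial showed no functional benefit overall.

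**Conclusion.** The point holds as one about how an assumption is stated and how the primary outcome is described. Independence is unsupported and doubtful, and one minus Kaplan-Meier will overstate the occlusion proportion patients experience. In the control arm, 35% on the Kaplan-Meier scale is about 30% if all of the planned 30% mortality occurs with the drain in place, and about 32-33% with 10-20% mortality in that period. These sizes assume constant hazards and leave removal out.

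The Cox hazard ratio remains valid as a cause-specific comparison and is unbiased under independence. Under assumed log-normal severity and a mortality difference, a null value drifts to about 1.02 to 1.25, against the arm with lower mortality. If that arm were IRRAflow, the article's threshold for an interesting beneficial finding would be harder to meet; if mortality were higher on IRRAflow, the drift would flatter the device. Either way it is small relative to what about 9 events can resolve. The sample size of 58 is not in question. For recurrent haemorrhage the issue is minor, because that outcome is descriptive only.

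**What to change.** - Replace the statement that occlusion is independent of mortality with an explicit assumption.
- Keep the log-rank test and Cox model as the primary comparison, and label it a comparison of cause-specific hazards.
- Describe occlusion by arm with Aalen-Johansen cumulative incidence curves, with death and drain removal without occlusion as competing events, and report the risk difference with its confidence interval.
- Do the same for recurrent haemorrhage, with death as the competing event.
- Add a Cox model adjusted for the Graeb score as a sensitivity analysis. With about 9 expected events it should carry this one covariate only and be read as supportive.

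The cost is some wording and a small amount of standard analysis. Deaths, duration of drainage and the Graeb score are already needed for endpoints or eligibility, so no new data are required. If the analysis plan already contains these analyses, only the wording needs to change.
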